## Abstract

Fathers play a unique and important role in shaping their children’s physical activity (PA), independent from the mother. Lifestyle interventions focusing simultaneously on PA of fathers and their children (“co-PA”) are therefore a novel and promising way to improve PA of both. A theory-based lifestyle intervention was co-created with fathers (i.e., the Run Daddy Run intervention), using the behavior change wheel as a theoretical framework. The aim of the present study is to describe the protocol of the Run Daddy Run intervention study, focusing on improving (co-)PA of fathers and children, and the prospected outcomes. The developed intervention consists of six (inter)active father-child sessions and an eHealth component, delivered over a 14-week intervention period. Baseline measurements will be conducted between November 2019–January 2020, post-test measurements in June 2020, and follow-up measurements in November 2020, with (co-)PA as the primary outcome variable. Outcomes will be measured using accelerometry and an online questionnaire. To evaluate the intervention, multilevel analyses will be conducted. This study will increase our understanding on whether a theory-based, co-created lifestyle intervention focusing exclusively on fathers and their children can improve their (co-)PA behavior and has important implications for future research and health policy, where targeting fathers might be a novel and effective approach to improve (co-)PA and associated health behaviors of both fathers and their children.

## 1. Introduction

Low levels of physical activity (PA) can be found in many European primary-school aged children. For example, 4.6% to 16.8% of the European primary school-aged children (10–12 years old) does not meet the international recommendation of at least 60 min of moderate-to-vigorous PA per day [1]. This is of concern, as low levels of PA are associated with negative physical and psychological health outcomes, including a higher risk of overweight and obesity [2]. Therefore, promoting PA in children has become an important focus in health promotion and obesity prevention research [3].

It is widely accepted that parents play an important role in establishing healthy lifestyle behaviors in their children, as well as in sports performance [4,5,6]. However, most studies have not distinguished between the differential influence of fathers and mothers on their children’s PA levels [7,8,9]. Yet, recent research indicates that fathers play a unique and important role in shaping their children’s health behaviors [10,11,12], especially PA. Studies have shown that both fathers’ weight status and PA levels are positively associated with their children’s weight status and PA levels, independently of the weight status and PA levels of the mother [12,13,14,15,16]. Moreover, a recent study including a sample of 934 European father-child dyads has shown that the association between fathers’ weight status and their children’s weight status is mediated by the level of PA of the father, through the level of PA of the child [17]. Indeed, studies have suggested that “active play” between father and child is more central to fathers’ parenting style than it is to mothers [18,19], and that this kind of play is advantageous for the motoric development of the child [16]. Furthermore, this kind of play may not only influence both fathers and children their PA behavior, but also the quality of their relationship and the psychosocial wellbeing of the child [20,21,22]. This suggests that focusing on PA of both the father and the child might be a potentially effective intervention strategy, as previous intervention studies have mostly engaged mothers while fathers have not been targeted [23,24]. A possible strategy could be to focus on “co-PA”, where the father and the child participate in PA together. Whereas mothers tend to play a larger role in the logistical planning of PA, fathers are more likely to engage in modelling PA [25,26]. Fathers spend more time with their child in unstructured, competitive, wrestling-style play (i.e., also referred to as ‘rough-and-tumble’ play), which is a form of play that is more vigorous and with greater physicality than that of mothers [25,26]. The modelling of vigorous and moderate-to-vigorous PA by fathers has been shown to be associated with higher levels of PA in their children [26,27].

According to our knowledge, only two programs have been developed specifically targeting fathers and children, which were both Australian. Healthy Dads Healthy Kids aimed to help overweight fathers lose weight and establish positive health behaviors for their children [10,28], whereas the DADEE (Dads and Daughters Exercised and Empowered) program aimed to promote PA between father and daughters [29,30] The results of these two Australian interventions showed that engaging fathers and children in co-PA increased both fathers’ and children’s (total) PA, positively influenced their weight status, improved the father-child relationship and the social-emotional well-being of the child. Further research is however necessary to better understand the effects of co-PA, and to confirm the abovementioned results in a European context. Using an experimental approach is thereby highly recommended [31,32]. Furthermore, it is not only important to investigate the effect of the intervention on (co-)PA of both fathers and children, but also the factors that determine (co-)PA, for example the parenting practices of the father, psychosocial determinants of (co-)PA such as attitude, self-efficacy and knowledge regarding (co-)PA and the family health climate regarding PA in the family. Literature has already shown that these factors play an important role, but were not yet sufficiently targeted in previous interventions [16].

Last, it is highly recommended that an intervention is grounded in and informed by a theoretical framework, in order to result in larger effect sizes [33,34]. Additionally, most lifestyle interventions do not seem to meet fathers’ needs and preferences [35], which results in low participation rates [36,37]. Therefore, the perspective of the fathers should be taken into account when developing an effective intervention [38]. Recently, there has been increased attention for using a co-creation approach in health promotion intervention studies [39,40,41]. The process of co-creation, which may be defined as a strong and active collaboration between end-users (i.e., fathers) and researchers [42], might be a promising approach to enhance effectiveness [43,44].

Taken together, this paper presents the study protocol for a co-created theory-based family-based lifestyle intervention (i.e., the Run Daddy Run intervention) whose main goal is to improve (co-)PA of fathers and their children, as well as other outcomes that are related to (co-)PA (i.e., its psychosocial determinants, sedentary behaviour (SB), parental practices, body Mass index (BMI), quality of the father-child relationship and the family health climate regarding PA). This study will increase our understanding on whether a theory-based, co-created lifestyle intervention focusing exclusively on fathers and their children can improve their (co-)PA and associated health behaviors. This has important implications for future research and health policy, where targeting fathers might be a novel and effective approach to improve health and health behaviors in children. The items addressed in this protocol paper are based on the 2013 Standard Protocol Items: Recommendations for Interventional Trials (SPIRIT) statement [45]. The completed SPIRIT Checklist has been included as Supplementary File S1. 

## 2. Materials and Methods

### 2.1. Development of the Run Daddy Run Intervention

The Behavior Change Wheel was used as a theoretical framework to systematically develop the intervention [46,47]. The intervention development process, modified and reproduced from ‘A Guide to Using the Behavior Change Wheel’ [47], follows three stages: (1) understanding the behavior, (2) translating findings into an intervention, and (3) refining and pre-testing the intervention, including 10 steps across the three different stages (see Table 1). Additionally, a co-creation approach was included in the intervention development process [41]. An overview of how this co-creation approach was combined with the behavior change wheel is presented in Table 1, where the main goal of each step is also described. The 10 steps were systematically followed where the completion of the tasks in one step created a product that was the guide for the subsequent step. More specifically, two co-creation groups with fathers were carried out. The first co-creation group (i.e., co-creation Group A) consisted of a group of five fathers (for descriptive statistics see Table 2), with whom four co-creation sessions were conducted between September–November 2018. Each of the four sessions lasted about 150 min and were facilitated by two researchers, who received a training by co-creation experts in using a co-creation approach to ensure effective delivery of, and engagement of the fathers during the sessions. Key principles in the development, implementation and evaluation of co-creation projects were followed during the entire development process [39,41]. The content of each of these co-creation sessions and its link with the different steps of the behavior change wheel can be found in Table 1. During these co-creation sessions, the intervention goals were selected and described, which were based on the barriers and motivators experienced by the fathers. In total, 13 intervention goals were described (see Table 3). These intervention goals were then linked by the researcher to the COM-B components and theoretical domains of the Theoretical Domain Framework (TDF) of the Behavior Change Wheel (for an overview see Supplementary File S2)

The intervention “concept” created by co-creation Group A was then presented to and fine-tuned by a second co-creation group (i.e., co-creation Group B), in December 2018. This co-creation group included five fathers with a lower socio-economic status and/or higher BMI (for descriptive statistics see Table 3) who were each separately interviewed to discuss and review, in detail, the end-result of the co-created intervention by Group A. The result of both co-creation groups was the Run Daddy Run intervention, which is a family-based lifestyle intervention, targeting (co-)PA of fathers and their primary-school aged children (6–8 years old) as the primary outcome, as well as its psychsocial determinants, SB, parental practices, BMI, quality of the father-child relationship and the family health climate regarding PA as secondary outcomes. As a last step of the intervention development process, the intervention was pre-tested in a pilot study among a group of 12 fathers and children to evaluate the created intervention for the first time and to make some final adjustments, of which the results will not be reported in the current study protocol.

For the co-creation sessions and interviews, fathers were recruited through convenience sampling, flyers and social media. Requirements to participate were; having at least one primary school-aged child (6–12 years old), speaking Dutch and having a smartphone with internet connection.

After each co-creation session/interview, participants were asked to complete a process evaluation questionnaire, enabling an evaluation of the session/interview given, and ensuring that the key principles of co-creation were met [39]. More specifically, participants were asked to give a score, ranging from 1 (weak) to 5 (excellent) on several dimensions important in co-creation (e.g., climate of trust and openness, equal influence on decision, being able to share opinion, etc.). In general, the mean scores of Group A on the dimensions ranged from 3.75–5 on a total score of 5, and in Group B from 4.25–4.75/5, suggesting that the co-creation sessions and interviews met the key principles of co-creation.

### 2.2. The Run Daddy Run Intervention

The main aim of the Run Daddy Run intervention was to increase (co-)PA by engaging fathers and children together in PA. Additionally, some components were added to target psychosocial determinants of (co-)PA, SB, and other health related components (i.e., PA family context, quality of father-child relationship and parental practices towards PA). The content of the intervention, created during the intervention development process, is described below.

#### 2.2.1. Content of the Run Daddy Run Intervention

The intervention consists of a face-to-face component, including six (inter)active sessions for fathers and their children, and an eHealth component. Both components will be delivered over a 14-week intervention period. A timeline of the total intervention period is presented in Figure 1. The sessions for will be delivered on a two-weekly basis, each session lasting 120 min. The last session will be delivered four weeks after the fifth (and thus second last) session, so that this session can serve as a follow-up session. All sessions will be guided by three facilitators (one main facilitator and two supporting facilitators, which are trained experts in movement and sports and/or health promotion sciences). The eHealth component will be used throughout the entire intervention period. Participants will be assigned to three different groups (based on their date- and time preferences), each including about 12 father-child dyads. Each group will receive a session on a different evening in the same week. All sessions will take place at a local school for convenience reasons.

Each session consists of a 40-min informative part (i.e., with some education and theory on a particular topic) and a 60-min active part. The timeline of such a session can be found in Figure 2. In the informative part, education and theory will be provided by a facilitator to the fathers on a particular theme that appeared to be important by fathers during the intervention development (see Table 4 for the different themes of the informative part). This will be done using an oral presentation with didactic slides. Children will work separately on that same theme with the other two other facilitators, using a child-friendly method (i.e., coloring task). Thereafter, co-PA goals will be set by the father-child dyads in group. These goals will be SMART: specific, measurable, attainable, realistic and timely (e.g., “on Saturday afternoon we will play soccer in our garden for 20 min”), which will yield a higher change of success in achieving them [48]. After setting these goals, they will be entered on their personal profile on the Run Daddy Run website, which will be described in more detail below.

After the informative part, fathers and children will move to the sports field/hall where the active part of the sessions will take place. The active part of the session (60 min) includes various exercises and activities for fathers and their children. More specifically, each session will include six different exercise components, with each session having two to four fundamental movement skills (FMS) as the main theme throughout the session (see Table 4 for the different themes of the active part). In Supplementary File S3, an overview of the different FMS practiced in each session can be found in more detail. An overview of the last component of the active part (i.e., the progress activity, with the aim to rehearse and perform better on all the FMS learned throughout the sessions) can be found in Supplementary File S4.

The online part of the intervention consists of a website (www.rundaddyrun.be (accessed on 14 January 2021)) with a profile that can be accessed by all participants with their personal login and password, during the entire 14-week intervention period. A visual representation of this personal platform can be found in Supplementary File S5. As eHealth components of an intervention are more effective when they include one or more behavior-change techniques (BCTs), the online platform will consist of the BCT goal setting, self-monitoring, shaping knowledge and instructions on how to perform the behavior. More specifically, fathers and children will be asked in each session (six times in total) to set a (SMART) co-PA goal, and log it on their personal profile. The aim will be to reach this co-PA goal by the next session, by performing and logging co-physical activities at home (i.e., self-monitoring). For a graphical representation of this logging process, see Figure 3. By logging activities performed together, participants will fill their “personal battery” (i.e., which is full when reaching the personal goal), as well as the “group battery” (i.e., which is full when all individual goals of the group are reached). In each subsequent session, goals will be evaluated and a new, modified goal will be set. The aim of this new goal is to find an optimal balance between achievable and challenging.

A third behavioral change component that is included in the online platform is shaping knowledge, including instructions on how to perform the behavior. More specifically, fathers and children will have access to a large variety of PA and exercise ideas that can be performed together, with concrete instructions. Additionally, also practical information can be found on this personal platform, such as data of the (inter)active sessions, documents and materials used in the sessions. Last, it is recommended in the literature to combine the usage of a website with a reminder system, such as automated emails or text messages to reinforce website use [49] in order to address the high levels of attrition that are negatively affecting many online interventions [50,51]. Therefore, the use of the personal platform on the website will be combined with a chat group in which each group of participants will be included based on their mobile phone number (after explicit permission), together with the facilitators of the (inter)active sessions. The main goal of this chat-message group is to create a positive group atmosphere and group dynamics, and for the facilitators to send reminders for settings goals and logging the performed activities.

#### 2.2.2. Participants

The Run Daddy Run intervention will include Belgian fathers and their primary school-aged children from the first, second and third year of primary school (6–8 years old). The first three years of primary school were targeted in order to optimize group homogeneity regarding cognitive and motor abilities of the children. Furthermore, younger children are more susceptible to behavior shaping compared to older children. The following inclusion criteria will be applied: being the (step) father and/or male primary caregiver of a child of 6–8 years old; being Dutch-speaking; being in good health; and having a mobile phone with internet access.

#### 2.2.3. Sample Size

Using the software GPower 3.0.10 (Universität Kiel, Kiel, Germany) [52], the required sample size was calculated. Based on the obtained effect sizes of previously implemented interventions for fathers and children targeting co-PA [52], a minimally detectable effect size of f = 0.20 was intended for the main PA outcome (i.e., co-PA) in the present study. This effect size was slightly more conservative than the obtained effect sizes for co-PA in the studies of Morgan et al. (i.e., n = 6 reported effect sizes across 3 studies, range f = 0.42–0.73, mean f = 0.58). This sample size calculation was based on 80% power to detect a significant difference in PA outcomes between groups, significance level alpha 0.05, having two groups (intervention and control group) and three measurements (pre-test, post-test and follow-up). The a priori power analysis suggested a total sample size of 42 families (fathers and children). Assuming an attrition rate of 20% [10], a total sample size of 51 fathers will be required.

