#### 2.2.4. Recruitment

For the intervention study, fathers and their primary school-aged children (6–8 years old) will be recruited in multiple ways through convenience sampling and snowball sampling. These methods of sampling will be used in order to reach a sufficient number of male participants, as research has indicated that it is difficult to engage fathers for lifestyle interventions [12,53]. More specifically, researchers will recruit fathers through contacting their acquaintances, friends and family. Fathers will also be recruited online, through social media and e-mail. Last, flyers and posters will be distributed in schools, sports clubs, libraries, etc. Additionally, snowball sampling will be used where registered fathers will be asked to contact their friends, family or acquaintances and invite them to participate in the intervention. The recruitment procedures will continue until the required number of participants is reached.

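### The recruitment target of 51 multiplies 42 by 1.2 instead of dividing by 0.8: 20% attrition calls for 53, and 51 does not obviously fit three session groups of about 12

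*Protocol article*

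**What the plan says.** Section 2.2.3 (Sample Size) gives these inputs: "a minimally detectable effect size of f = 0.20 was intended for the main PA outcome", a calculation with "This sample size calculation was based on 80% power to detect a significant difference in PA outcomes between groups", "significance level alpha 0.05", and "having two groups (intervention and control group) and three measurements (pre-test, post-test and follow-up". The result is reported as follows: "The a priori power analysis suggested a total sample size of 42 families (fathers and children"). The allowance for loss comes next: "Assuming an attrition rate of 20% [10], a total sample size of 51 fathers will be required".

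Two other sections bear on the number. Section 2.2.1, on delivery of the intervention: "Participants will be assigned to three different groups (based on their date- and time preferences), each including about 12 father-child dyads". Section 2.2.4, on when recruitment ends: "The recruitment procedures will continue until the required number of participants is reached".

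The text states no allocation ratio and no size for the control group. Section 2.2.5 says that participants are not randomised and that the control group is recruited before the intervention group.

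**The concern.** The target is meant to leave 42 families after a fifth of those recruited are lost. A fifth of 51 is about 10, which leaves 40 or 41, so the target fails on the section's own two inputs. Recruitment runs until the required number is reached, so an error in that number carries straight into the size of the study. What is at stake is the statement of 80% power after 20% attrition.

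There is also a question of fit between sections. The 42 can be reproduced with equal arms, yet three session groups of about 12 make an intervention arm of about 36, well over half of 51. For a given total, unequal arms give less power than equal ones.

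**Working it through.** **Inputs from Section 2.2.3:** f = 0.20, α = 0.05, power 80%, k = 2 groups, m = 3 measurements, 42 families, 20% attrition, target 51. **From Section 2.2.1:** three groups of about 12 dyads.

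**Assumed, because the article does not state them:** the test is the group-by-time (within-between) interaction, the correlation between repeated measurements is ρ = 0.5, sphericity holds (ε = 1), and the arms are equal.

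**Step 1. Reproduce the 42.** The noncentrality is λ = f² × N × m / (1 − ρ), with (k − 1)(m − 1) = 2 and (N − k)(m − 1) degrees of freedom.

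- N = 42: λ = 0.04 × 42 × 3 / 0.5 = 10.08, with 2 and 80 degrees of freedom; power 80.3%.
- N = 41: λ = 9.84; power 79.3%.
- N = 40: λ = 9.60; power 78.2%.

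So 42 is the smallest N that reaches 80%. Other correlations do not give it: with even N, ρ = 0.3 requires 58 and ρ = 0.7 requires 26. A test of the between-group main effect at ρ = 0.5 requires 134. The assumed inputs are therefore very likely those used.

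**Step 2. Reproduce the 51.**

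- Multiplying: 42 × (1 + 0.20) = 50.4, rounded up to 51. This matches.
- Dividing: 42 / (1 − 0.20) = 52.5, rounded up to 53. This does not match.

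**Step 3. Check each target against the requirement.**

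- 51 × 0.8 = 40.8, so 40 or 41 families remain, below 42.
- 53 × 0.8 = 42.4, which meets 42. Equal arms need an even total, so 54 (27 + 27).
- Attrition that 51 can absorb: 1 − 42/51 = 17.6%.
- Power with 40 or 41 remaining, from Step 1: 78.2% or 79.3%.

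**Step 4. Set the target beside the delivery plan.** 3 × 12 = 36 intervention dyads. Equal arms within 51 would be 25 or 26 each, or about 8 or 9 dyads per session group (51 / 2 / 3 = 8.5). The two figures fit only if the arms are unequal, the total exceeds 51, or the session groups are smaller than about 12.

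**Step 5. A conditional illustration only.** If the total were held at 51 and the intervention arm filled to 36, there would be 51 − 36 = 15 controls. At 20% loss, 36 × 0.8 = 28.8 and 15 × 0.8 = 12, so about 29 and 12 remain. The equivalent size in equal arms is 4 × 29 × 12 / 41 = 33.95, which gives λ = 0.04 × 33.95 × 3 / 0.5 = 8.15 and power of about 71%. With ρ between 0.4 and 0.6, the result runs from 62% to 81%.

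**The case against.** **The shortfall is smaller than the uncertainty in the inputs.** In the same model, 41 families give 80.1% if ρ is 0.51 instead of 0.50, and 40 families give 80.3% if f is 0.205 instead of 0.20. Section 2.2.3 also sets f = 0.20 against earlier effects that it reports as 0.42 to 0.73. The multilevel analysis in Section 2.2.8 can in general use families with partial follow-up, so counting completers only may overstate the loss. All of this stands, and it is why the point is minor. It does not make 51 the right result from 42 and 20%.

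**The arm sizes are not stated.** A reader might infer that the plan has only 15 controls and about 71% power. The documents do not support that. Section 2.2.1 gives an approximate group size for the sessions, not an enrolment quota. The total in Section 2.2.3 is a requirement, not a ceiling. The control group is recruited first, so it is not what remains once the intervention places are filled. The text would equally allow about 36 per arm, with a total well above 51. Section 2.2.5 also refers to Figure 4 for the study flow, and that figure was not available for this review; it may give arm sizes. This objection stands in full against any claim of a particular imbalance. What survives is that about 36 in one arm and equal arms within 51 do not go together, and the text does not say how they are reconciled.

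**Conclusion.** The target of 51 is wrong as written, and the error is minor. Given 42 families and 20% attrition, the total is 53, or 54 for equal arms. That conclusion is arithmetic on two stated numbers and needs no assumption. The article does not print its inflation formula, so multiplication by 1.2 is inferred from the exact match.

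The cost is two families, or power of about 78–79% against the stated 80%. The power figures rest on the assumed interaction test, ρ = 0.5, ε = 1 and equal arms, which together reproduce the 42. No conclusion of the study is likely to turn on the difference.

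The arm-size point is secondary and supports only a request to reconcile Sections 2.2.1 and 2.2.3. The 71% figure belongs to a split that the documents do not state and depends heavily on the correlation, so it should not be read as the power of this plan.

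**What to change.** In Section 2.2.3, replace 51 with 53, showing 42/0.8 = 52.5 (or 54 if equal arms are intended). Alternatively, keep 51 and restate it as about 78–79% power at 20% attrition, or as 80% power at up to 17.6% attrition. Give the assumed correlation and the test beside it, since the power figures depend on them.

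Add one sentence that reconciles the total with the three session groups of about 12 in Section 2.2.1 by giving the planned number in each arm. If the planned split is unequal, state the power for that split.

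The cost is one corrected number and one sentence, with either two more families (three for equal arms) or a slightly lower stated power. Neither the design nor the analysis changes.
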